### Inclusion criteria

2.3

Participants who meet all the following requirements will be enrolled:

(1)  Female patients aged 20–85 years.(2)  Patients scheduled for elective radical mastectomy.(3)  Preoperative patients with Hamilton Anxiety Rating Scale (HAMA) scores ≥7 measured before intervention.(4)  Patients with elementary school education or above, and normal communication, hearing, and comprehension abilities.(5)  Participants who voluntarily signed informed consent forms.(6)  Patients classified as American Society of Anesthesiologists (ASA) Physical Status I–III.

### Exclusion criteria

2.4

Participants who meet one of the following requirements will be excluded:

(1)  History of neurological disorders or psychiatric disorders (with drug treatment).(2)  Severe cardiovascular or cerebrovascular diseases.(3)  Contraindications for taVNS: recent auricular trauma, skin lesions, erythema, or infection in the auricular region; presence of implantable electrophysiological devices (e.g., cardiac pacemakers, stents, or prosthetic joints).(4)  Chronic use of psychotropic medications (e.g., corticosteroids, antidepressants, or anxiolytics).

### Criteria for discontinuation

2.5

During this trial, subjects experiencing the following conditions will be considered as dropout cases, and the reason and date of dropout will be recorded in a case report form.

(1)  Intraoperative blood pressure or heart rate could not be maintained, or severe intraoperative complications occurred (e.g., hemorrhagic/anaphylactic shock, cardiac arrest, etc.).(2)  Patients who refused to undergo relevant scale assessments.(3)  Incomplete HRV monitoring data.(4)  Loss to follow-up.

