### Sample size

2.2

According to the Chinese Guidelines for the Prevention and Treatment of Anxiety Disorders, which define “a response rate ≥50% as effective and <30% as ineffective.” This study hypothesized response rates of 50% in the treatment group and 30% in the control group. With a statistical power of 0.80 and a significance level of 0.05, sample size calculation using PASS 15.0 software indicated that 91 patients will be required per group. Accounting for a 10% dropout rate, we plan to enroll 101 participants per group, totaling 202 subjects.

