### Primary outcome

4.1

The primary outcome is perioperative anxiety alleviation rate in patients subjected to either full-course taVNS or sham stimulation before the first intervention and after the last intervention. The anxiety alleviation rate will be calculated as follows: (baseline score − post-intervention score)/baseline score × 100%.

Perioperative anxiety will be assessed using the Hamilton Anxiety Rating Scale (HAMA), a 14-item scale with a total score ranging from 0 to 56. The severity of anxiety will be categorized as follows: total score <7: no anxiety; total score 7–13: mild anxiety; total score 14–20: moderate anxiety; total score >20: severe anxiety.

Patient anxiety will be assessed before (T0) and after (T1) the initial taVNS or sham stimulation. Further assessments occurr at 2 h post-surgery (T2), following the intervention on postoperative days 1 to 3 (T3–T5), and at 30 day after surgery (T6).

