#### Clinical examination assessment indicators

4.2.2

*Heart rate variability (T0 to T5)*: Heart rate variability (HRV) parameters, including low-frequency power (LF), high-frequency power (HF), the ratio of LF to HF (LF/HF), the standard deviation of normal-to-normal intervals (SDNN), the standard deviation of the average NN intervals extracted for each 5-min segment (SDANN), and the percentage of adjacent NN intervals differing by more than 50 ms (pNN50), will be measured using an autonomic nervous function analyzer (ZSY-1, Shenyang Weijin).

Under the assistance of nursing staff, HRV measurements will be obtained from conscious, seated patients during a standardized morning window (8:00 to 11:00). During the test, the patient maintain calm breathing while holding a sensor fixed in the palm for 5 min to obtain HRV data, which transmit to a computer for analysis.

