## Statistical analysis

6

Statistical analysis will be performed using SPSS 23.0 (IBM Corp, Armonk, NY, United States). The normality of continuous variables was assessed using the Kolmogorov–Smirnov (K–S) test. Normally distributed data were expressed as mean ± standard deviation (SD). One-way analysis of variance (ANOVA) was employed for multiple group comparisons, while the independent t-test was used for pairwise comparisons between groups. Paired *t*-test was applied for within-group comparisons. Non-normally distributed data were presented as median (interquartile range) and analyzed using nonparametric rank-sum tests. Categorical variables were compared using the chi-square test. A two-tailed *p*-value <0.05 was considered statistically significant.

The primary outcome measure will be analyzed using the intention-to-treat (ITT) principle. Missing data for the primary outcome were handled using multiple imputation by chained equations under the missing-at-random assumption. The interpolation model includes all the analytical variables as well as any auxiliary variables that may be related to the detachment. We generated imputed datasets using the mice package in R. The results from the imputed datasets were combined using Rubin’s rules.

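### The dropout criteria and the full-course wording are not reconciled with the ITT primary analysis, so HAMA scores that were observed could be discarded or needlessly imputed

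*Protocol article*

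**What the plan says.** Four places in the protocol article bear on who counts in the primary analysis.

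- **Section 2.5, Criteria for discontinuation.** It states that "subjects experiencing the following conditions will be considered as dropout cases", with reason and date entered on the case report form. The conditions include "Intraoperative blood pressure or heart rate could not be maintained, or severe intraoperative complications occurred" and, as item (3), "Incomplete HRV monitoring data". Refused scale assessments and loss to follow-up complete the list.
- **Section 4.1, Primary outcome.** The outcome is the "perioperative anxiety alleviation rate in patients subjected to either full-course taVNS or sham stimulation", comparing HAMA before the first session with HAMA after the last. The abstract uses similar wording.
- **Section 6, Statistical analysis.** "The primary outcome measure will be analyzed using the intention-to-treat (ITT) principle". Then: "Missing data for the primary outcome were handled using multiple imputation by chained equations under the missing-at-random assumption".
- **Section 2.2, Sample size.** 91 per group are required, raised to 101 for 10% dropout, 202 in total.

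None of these says whether a section 2.5 dropout, or a patient who missed a session, stays in the ITT set, or whether HAMA scores already recorded for that patient are used.

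**The concern.** Item (3) ties a patient's status in the trial to a secondary measure. Someone with every HAMA score recorded becomes a dropout because one HRV recording failed. If that status carries over to the primary outcome, real data are deleted or replaced by imputed values for no reason.

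Item (1) raises a different problem. The first session is given 30 min before induction (section 3), so intraoperative instability comes after randomisation and after exposure. The article describes taVNS as acting on autonomic function and lists bradycardia among the adverse events to record (section 5.2). It does not link bradycardia to item (1), but a dependence of removal on arm cannot be ruled out. Taking patients out of a comparison on such an event gives up the protection of randomisation.

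The full-course phrase can be read as a third filter, limiting the primary outcome to completers. What is at stake is that the primary set could be settled after the data are seen.

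**Working it through.** **1. The plan's own figure.** Inputs from section 2.2: "This study hypothesized response rates of 50% in the treatment group and 30% in the control group", power 0.80, alpha 0.05 (two-sided, section 6), 1:1 allocation. Unpooled normal approximation:

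n = (1.960 + 0.842)² × (0.5×0.5 + 0.3×0.7) / 0.2² = 7.849 × 0.46 / 0.04 = 90.26, so 91 per group.

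Dropout: 91 / 0.9 = 101.1, stated as 101. The figures reproduce (a pooled-variance formula gives 93), so this point does not rest on a sample size error.

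**2. How many patients item (3) could catch.** Table 1 and section 4.2.2 schedule HRV at six time points, T0 to T5. The documents give no miss rate, so m per time point is assumed. *Incomplete* is not defined; here it is taken as any one of the six missing, with misses independent:

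P(incomplete) = 1 − (1 − m)⁶

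The 10% allowance is used up when m = 1 − 0.9^(1/6) = 0.0174, about 1.7%.

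**3. Power if those patients were deleted.** On the response-rate basis of section 2.2, with pooled variance under the null and n per arm:

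power = Φ[(0.2√n − 1.960 × √(2×0.4×0.6)) / √0.46]

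For n = 101: (2.010 − 1.358) / 0.678 = 0.961, so power is 83.2%.

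| Assumed m | Loss, independent misses | n per arm left | Power | Loss, full clustering |
|---|---|---|---|---|
| 1% | 5.9% | 95.1 | 80.9% | 1% |
| 2% | 11.4% | 89.5 | 78.4% | 2% |
| 3% | 16.7% | 84.1 | 75.9% | 3% |
| 5% | 26.5% | 74.2 | 70.5% | 5% |

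The last column is the other extreme: the same patients miss every recording, so the share of patients lost equals m. Even at 5% that leaves 101 × 0.95 = 95.95 per arm and power of about 81%. At the planned 10% loss (90 per arm) power by this formula is 78.7%.

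One feature of the schedule bears on how likely misses are. Section 4.2.2 says "HRV measurements will be obtained from conscious, seated patients during a standardized morning window (8:00 to 11:00"). T2 is 2 h after surgery, so a T2 recording inside the window needs surgery to end by 11:00 − 2 h = 9:00. The article does not say whether a recording outside the window counts as incomplete, and the table does not build this in.

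**4. What arm-dependent removal could do.** Every input here is assumed. Take no true effect, response rate p in both arms, 101 per arm and a fraction d = 10% removed from each. In one arm those removed respond at rate q; in the other they are typical. The rate left in the first arm is (p − dq) / (1 − d).

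- p = 30%, q = 15%: (0.30 − 0.015) / 0.9 = 31.7%, a spurious 1.7 points; type I error 5.7%.
- p = 40%, q = 0: 0.40 / 0.9 = 44.4%, a spurious 4.4 points; type I error 9.3%.

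If removal is unrelated to outcome and arm, there is no bias and the cost is power.

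**The case against.** The strongest reply is that being a dropout and being in the ITT set are compatible. Section 2.5 labels patients and records why. It does not say that they leave the analysis, that their HAMA scores are discarded, or that HAMA collection stops. Section 6 is the analysis rule, and multiple imputation exists for such patients. A reader might infer that they are excluded, or that the three rules cannot all be followed; the text shows neither. It is true that section 2.2 uses the same word for patients lost from the required number, which points towards non-contribution, but that is an inference.

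The full-course phrase can also be read as the measurement span: change over the whole course, not after a single session. The abstract's explanation (after the final session against before the first) supports that reading. A completer population is a possible reading, not a stated rule.

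A reader might further infer that dropout status hides harm. The documents do not support this: reason and date go on the case report form, Table 1 records adverse events until discharge, and section 5.2 covers events related and unrelated to taVNS.

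Finally, the larger losses and the reduced power need independent misses, a strict meaning of *incomplete*, and deletion of those patients, which section 6 does not describe.

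All of this limits the point without removing it. Even if imputation brings dropouts back, applying item (3) to the primary outcome would put imputed values in place of observed HAMA scores. That is a badly fixed rule, not detail left to a fuller document.

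**Conclusion.** The concern stands as a failure to reconcile sections 2.5, 4.1 and 6 and the abstract. Incomplete HRV should not decide a patient's status for a HAMA outcome, and a post-randomisation intraoperative event should not decide membership of an ITT set.

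The consequences are conditional on the dropout rule being carried into the primary analysis. In that case observed HAMA data are lost or needlessly imputed, and removal could differ by arm. The documents give neither size nor direction for any bias; the 1.7 to 4.4 points above are illustration only. The HRV loss runs from 1–5% of patients (full clustering) to 5.9–26.5% (independent misses) for assumed miss rates of 1–5% per time point. Power of about 76% and 70% at 3% and 5% applies only to the independent case with deletion; keeping all 101 per arm gives about 83%.

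**What to change.** Amend the wording so that sections 2.5, 4.1 and 6 and the abstract agree, before unblinding:

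1. Remove item (3) from section 2.5. Incomplete HRV then affects only the HRV analyses.
2. State that meeting a section 2.5 condition, or missing sessions, does not end HAMA collection where assessment is possible and does not take the patient out of the primary analysis.
3. Define the primary set as all randomised patients, in the arm to which they were randomised, with multiple imputation only where the post-intervention HAMA is truly missing.
4. Say that full-course gives the measurement span, or move it to a named supportive per-protocol analysis.

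This concerns follow-up and analysis only. Whether stimulation stops after an intraoperative event is for the sponsor to decide. The planned number does not change. The cost is a wording amendment and a few more HAMA follow-ups in patients already enrolled.

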### Randomization and blinding

2.6

Participants will be randomly assigned in a 1:1 ratio to either the treatment group (taVNS group) or the control group (sham stimulation group) based on a computer-generated randomization table. Allocation information will be sealed in opaque envelopes and will remain concealed until the intervention be administered by investigators prior to surgery. Outcome assessors, data processing personnel, other healthcare providers, and patients will be blinded to treatment allocation.

## Procedure

3

Participants will be screened from the elective surgery roster by the research team. At 30 min prior to anesthesia induction and at the same time point daily for postoperative days 1–3, patients will be subjected to either taVNS (treatment group) or sham stimulation (control group).

*Treatment group*: Electrical stimulation will be applied through electrodes placed on the cymba conchae. Following clip placement, taVNS will be administered for 30 min per session. The device will be activated with the following parameters:

Waveform: Dense-disperse wave.Mode: Constant voltage.Frequency: 20 Hz.Pulse width: 0.2 ms.Intensity: Subthreshold current (maximally tolerated without eliciting sharp pain).

*Control group*: The electrodes will be positioned identically, and the current will be increased over 30 s until the participant reported a tingling sensation. Then reduced to a level just below this perceptual threshold. The device remain off for the subsequent 30 min to simulate the sham condition (12).

## Outcome

4

### Primary outcome

4.1

The primary outcome is perioperative anxiety alleviation rate in patients subjected to either full-course taVNS or sham stimulation before the first intervention and after the last intervention. The anxiety alleviation rate will be calculated as follows: (baseline score − post-intervention score)/baseline score × 100%.

Perioperative anxiety will be assessed using the Hamilton Anxiety Rating Scale (HAMA), a 14-item scale with a total score ranging from 0 to 56. The severity of anxiety will be categorized as follows: total score <7: no anxiety; total score 7–13: mild anxiety; total score 14–20: moderate anxiety; total score >20: severe anxiety.

Patient anxiety will be assessed before (T0) and after (T1) the initial taVNS or sham stimulation. Further assessments occurr at 2 h post-surgery (T2), following the intervention on postoperative days 1 to 3 (T3–T5), and at 30 day after surgery (T6).

### Secondary outcome

4.2

#### Clinical symptom assessment indicators

4.2.1

(1)  Hamilton Anxiety Rating Scale (HAMA) (T0 to T6).(2)  Sleep quality score (T3 to T5): assessed using the Pittsburgh Sleep Quality Index (PSQI), with scores ranging from 0 to 21 (higher scores indicate poorer sleep quality).(3)  Incidence of postoperative delirium (T2 to T5): evaluated using the 3-Minute Diagnostic Interview for Confusion Assessment Method-Defined Delirium (CAM-3D).(4)  Pain score (T2 to T5): measured via the Numeric Rating Scale (NRS), ranging from 0 (no pain) to 10 (most severe pain).(5)  Frailty score (T3 to T5): assessed using the Fatigue, Resistance, Ambulation, Illnesses, and Loss of Weight (FRAIL), with scores ranging from 0 (most robust) to 5 (most frail).

#### Clinical examination assessment indicators

4.2.2

*Heart rate variability (T0 to T5)*: Heart rate variability (HRV) parameters, including low-frequency power (LF), high-frequency power (HF), the ratio of LF to HF (LF/HF), the standard deviation of normal-to-normal intervals (SDNN), the standard deviation of the average NN intervals extracted for each 5-min segment (SDANN), and the percentage of adjacent NN intervals differing by more than 50 ms (pNN50), will be measured using an autonomic nervous function analyzer (ZSY-1, Shenyang Weijin).

Under the assistance of nursing staff, HRV measurements will be obtained from conscious, seated patients during a standardized morning window (8:00 to 11:00). During the test, the patient maintain calm breathing while holding a sensor fixed in the palm for 5 min to obtain HRV data, which transmit to a computer for analysis.

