### Study design

2.1

This prospective randomized controlled trial will enroll 202 patients scheduled for radical mastectomy at our institution. Using a computer-generated randomization table, eligible participants will be allocated in a 1:1 ratio to either the treatment group (taVNS group) or the control group (sham stimulation group). The trial flow chart is shown in Figure 1. All participant characteristics and clinical outcomes will be documented using case report forms (CRFs). Data collection procedures are outlined in Table 1.

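### SDANN is listed as an HRV outcome at T0 to T5, but the 5-min recording prescribed per test holds only one 5-min segment, so SDANN as defined cannot be computed

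*Protocol article*

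**What the plan says.** All the relevant text is in section 4.2.2 of the protocol article (Clinical examination assessment indicators).

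- **Timing.** The outcome is headed "Heart rate variability (T0 to T5"), which is six assessments. Table 1 marks HRV at the same six time points.
- **Parameters.** Six are named: LF, HF, LF/HF, SDNN, SDANN and pNN50. SDANN is spelled out as "the standard deviation of the average NN intervals extracted for each 5-min segment (SDANN").
- **Recording.** At each test the patient breathes calmly while "holding a sensor fixed in the palm for 5 min to obtain HRV data".
- **Setting.** "HRV measurements will be obtained from conscious, seated patients during a standardized morning window (8:00 to 11:00").

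The article describes no longer, ambulatory or repeated recording anywhere.

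**The concern.** SDANN measures variation between segments: average the NN intervals within each 5-min segment, then take the standard deviation of those averages. It needs at least two segments. The protocol fixes the segment length and the recording length at the same value, so there is nothing for the averages to vary over.

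This is a conflict between two things the protocol does state, not a detail that an article leaves to a fuller document. An analysis plan cannot derive a between-segment quantity from one segment.

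HRV carries the trial's mechanistic aim (Introduction and Discussion). If the section is followed exactly, one listed parameter will be empty, constant at 0, or filled with some other quantity under the SDANN label. In the last case, a result could be published as a prespecified outcome that it is not.

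**Working it through.** The protocol states no figure for SDANN, so there is none to reproduce. The check is a count of segments.

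**Inputs** (all from section 4.2.2)

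- Segment length in the SDANN definition: 5 min.
- Recording length per test: L = 5 min.
- Assessments: T0, T1, T2, T3, T4 and T5, so 6.
- HRV parameters named: 6.

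**Formula**

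Number of segments: k = L / 5. With segment means m₁, …, m_k and their average m̄,

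SDANN = √[ Σ(m_j − m̄)² / (k − 1) ], with k − 1 degrees of freedom.

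**Numbers put in**

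1. k = 5 / 5 = 1.
2. With one segment, m̄ = m₁, so the sum of squares is 0.
3. With divisor k − 1 = 0 the result is 0/0, which is undefined.
4. With divisor k = 1 the result is √(0/1) = 0 for every patient at every visit, whatever the heart rhythm.

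**How long a recording would have to be**

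| Recording | Segments k | Degrees of freedom k − 1 |
|---|---|---|
| 5 min (as prescribed) | 1 | 0 |
| 10 min | 2 | 1 |
| 30 min | 6 | 5 |
| 24 h | 288 | 287 |

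Any value at all needs at least 10 min, and 10 min leaves a single degree of freedom.

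**Extent**

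- SDANN is unobtainable at 6 of 6 visits and is 1 of 6 named parameters.
- The remaining five (LF, HF, LF/HF, SDNN, pNN50) are not built from 5-min segment means and can be computed from one 5-min series.
- The sample size does not involve HRV. It rests on response rates: "This study hypothesized response rates of 50% in the treatment group and 30% in the control group". With two-sided alpha 0.05 and power 0.80, the unpooled two-proportion formula gives (1.960 + 0.842)² × (0.25 + 0.21) / 0.04 = 90.3, rounded up to the stated 91 per group. SDANN enters nowhere.

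**The case against.** **Could another reading rescue SDANN?** Three can be tried.

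- *The recording lasts through the morning window.* From 8:00 to 11:00 is 180 min, which would hold 36 segments. But the window says when the test takes place. The test itself is a seated 5-min sensor hold.
- *The six 5-min averages are pooled over T0 to T5.* That would give one value per patient, whereas the section and Table 1 make HRV an outcome at each time point.
- *The analyzer divides the 5 min into shorter pieces.* That contradicts the stated 5-min definition, and the resulting number would be a different index.

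The text supports none of these, so the core point stands.

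**How much does it matter?** Here the other side is largely right. SDANN is one index within one secondary outcome. The primary outcome is based on HAMA, no decision rule depends on SDANN, and conclusions about autonomic function can rest on the other five indices.

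**Stronger readings that a reader might infer**

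- *Every patient becomes a dropout.* Section 2.5 counts patients whose HRV monitoring is incomplete as dropouts, and one could argue that a field which can never be filled meets that condition. The natural meaning is a missing or interrupted recording. Nothing in section 2.5 says that one derived index that cannot be computed makes the monitoring incomplete.
- *The device must be using hidden sub-segments.* The protocol gives only the analyzer's model and maker, not its algorithm. A printed value might come from shorter segments, or might be a 0 from the population divisor.
- *A fixed share of the HRV comparisons is void.* Six parameters at five post-baseline visits would make 30 tests, 5 of them on SDANN. But section 6 lists tests generically and does not say which visits or contrasts apply to HRV, so the protocol does not support a count of comparisons.

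**Conclusion.** The point holds as an internal contradiction within section 4.2.2. The SDANN definition and the prescribed recording length cannot both stand, and SDANN is undefined or identically 0 at all six visits. Whatever the analyzer prints under that name could not be the quantity the protocol defines.

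The size is modest: one of six HRV parameters in a secondary, mechanistic outcome. The primary outcome, the sample size and the other five parameters are untouched. The documents do not support a claim about mass dropout, about how the device works, or about a number of lost comparisons.

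The conclusion rests on one assumption: that each assessment consists of one 5-min hold. The section does not use the word single, but it describes one hold per test and nothing else.

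**What to change.** Delete SDANN from the parameter list in section 4.2.2 and from the case report form. If the analyzer in fact reports a different short-segment index that the sponsor wants to keep, name that index, state its segment length and define it in place of SDANN. RMSSD (root mean square of successive differences), computed from the same 5-min NN series, is an optional substitute and not a necessary part of the correction.

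Lengthening the recording to hold several 5-min segments would also remove the contradiction. It would, however, change the measurement at six visits in a trial already recruiting, for the sake of one secondary index.

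**Cost.** Deletion or renaming changes one line of the protocol and one field of the case report form, and needs no new measurement. It is still a mid-trial change to a listed outcome parameter: recruitment began in August 2025 with completion expected in August 2026, and the trial is registered. It should therefore be a dated, documented amendment made before the HRV data are analysed.

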**Figure 1 fig1:**
[figure not shown]
Flow chart of the study. taVNS, transcutaneous auricular vagus nerve stimulation; HAMA, Hamilton Anxiety Rating Scale; PSQI, Pittsburgh Sleep Quality Index; CAM-3D, 3-Minute Diagnostic Interview for Confusion Assessment Method-Defined Delirium; NRS, Numerical Rating Scale; FRAIL, Fatigue, Resistance, Ambulation, Illnesses, and Loss of Weight; HRV, heart rate variability.

**Table 1 tab1:** Schedule of enrolment, interventions, and assessments.

Procedure	Study period						
	T0	T1	T2	T3	T4	T5	T6
Enrolment							
Eligibility screen	✓						
Informed consent	✓						
Allocation	✓						
Randomization	✓						
Interventions							
taVNS							
Sham stimulation							
Assessments							
HAMA	✓	✓	✓	✓	✓	✓	✓
CAM-3D			✓	✓	✓	✓	
NRS			✓	✓	✓	✓	
FRAIL				✓	✓	✓	
PSQI				✓	✓	✓	
HRV	✓	✓	✓	✓	✓	✓	
Adverse events	Throughout the study period until discharge						

taVNS, transcutaneous auricular vagus nerve stimulation; HAMA, Hamilton Anxiety Rating Scale; PSQI, Pittsburgh Sleep Quality Index; CAM-3D, 3-Minute Diagnostic Interview for Confusion Assessment Method-Defined Delirium; NRS, Numerical Rating Scale; FRAIL, Fatigue, Resistance, Ambulation, Illnesses, and Loss of Weight; HRV, heart rate variability. T0, before the initial taVNS or sham stimulation; T1, after the initial taVNS or sham stimulation; T2, 2 h after surgery; T3, 1 day after surgery; T4, 2 day after surgery; T5, 3 day after surgery; T6, 30 day after surgery.

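### The HRV recording at T2 (2 h after surgery) fits the 8:00–11:00 window only if surgery ends by about 08:55, so on an ordinary daytime list most T2 recordings will be out of window or not taken

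*Protocol article*

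**What the plan says.** All references are to the protocol article.

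- **Schedule.** Section 4.2.2 heads the measure "Heart rate variability (T0 to T5", and Table 1 ticks HRV at each of those six visits. The Table 1 footnote defines "T2, 2 h after surgery" and prints no tolerance.
- **Recording conditions.** Section 4.2.2 states that "HRV measurements will be obtained from conscious, seated patients during a standardized morning window (8:00 to 11:00". The patient is "holding a sensor fixed in the palm for 5 min to obtain HRV data". No visit is exempted from the clock window or the seated posture.
- **First stimulation.** Section 3 places it "At 30 min prior to anesthesia induction and at the same time point daily for postoperative days 1–3", and "taVNS will be administered for 30 min per session". T0 and T1 lie immediately before and after this first session.
- **Dropout.** Section 2.5(3) lists "Incomplete HRV monitoring data" among the conditions that make a participant a dropout case, with reason and date recorded.
- **Analysis.** Section 6 applies intention to treat with multiple imputation to the primary outcome, and lists paired t-tests for within-group comparisons in general terms.

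**The concern.** T2 is tied to the end of the operation, while the window is tied to the clock. The two rules can both be met only for operations that finish very early in the day. On other days staff must choose which rule to break, and the article does not say which.

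If they keep the window, the T2 recording is not taken, and section 2.5(3) can be read as making that patient a dropout. If they keep the 2 h timing, T2 is recorded at a different time of day, soon after anaesthesia and possibly not seated. Any T0-to-T2 change within an arm then mixes those conditions with autonomic recovery. If different staff choose differently, the T2 data are a mixture of both.

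This matters because section 7 presents HRV as the trial's objective measure, and the window evidently exists to standardise the conditions of recording.

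**Working it through.** **Inputs from the article:** window 8:00–11:00 (180 min); recording 5 min; session 30 min; T2 at 120 min after surgery; T1 after the first session and before induction.

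**Step 1. T2 alone.** Latest start of a recording finished by 11:00: 11:00 − 5 min = 10:55. Latest end of surgery: 10:55 − 120 min = 08:55. Earliest end of surgery: 8:00 − 120 min = 06:00. T2 therefore complies only if surgery ends between 06:00 and 08:55.

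**Step 2. T1 and T2 both in the window, T0 on an earlier morning.** Time left for induction plus surgery: 180 − (5 + 120 + 5) = 50 min. On the clock: T1 8:00–8:05, induction 8:05, surgery ends by 08:55.

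**Step 3. T0, T1 and T2 all in the same morning's window.** Time left: 180 − (5 + 30 + 5 + 120 + 5) = 15 min. On the clock: T0 8:00–8:05, session 8:05–8:35, T1 8:35–8:40, induction 8:40, surgery ends by 08:55.

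Steps 2 and 3 place the T1 recording between the end of the session and induction, so stimulation starts 35 min before induction. A 30-min session begun exactly 30 min before induction leaves no gap for T1. If T1 is left out and only T0 and T2 share the morning, the time left is 180 − (5 + 30 + 120 + 5) = 20 min.

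**Step 4. Range of operating times (assumed).** Section 5.1 says surgical duration will be recorded, but the article gives no expected duration or start time. The third column takes the earliest induction that keeps T1 in the window (8:05) and adds the duration plus 120 min.

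| Assumed induction to end of surgery | Latest induction for T2 to comply | Earliest T2 start if T1 is in the window |
|---|---|---|
| 60 min | 07:55 | 11:05 |
| 90 min | 07:25 | 11:35 |
| 120 min | 06:55 | 12:05 |
| 180 min | 05:55 | 13:05 |

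At every assumed duration, an induction early enough to rescue T2 comes before 8:05 and so puts T1 outside the window. T1 also leaves the window for any case induced after about 11:00.

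**Step 5. How much of the HRV outcome is touched.** Six parameters (LF, HF, LF/HF, SDNN, SDANN, pNN50) × six visits (T0–T5) = 36 results. T2 accounts for 6 of them, or 6/36 = 17%.

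**Step 6. The dropout allowance.** Section 2.2 needs 91 per group. With 50% against 30%, two-sided 0.05 and power 0.80, the unpooled formula gives (1.960 + 0.842)² × (0.25 + 0.21)/0.20² = 90.3, so 91, which reproduces the plan's figure. Enrolling 101 per group leaves room for 202 − 182 = 20 dropouts. If untaken T2 recordings were counted as dropouts, 21 such patients would exceed that allowance. This concerns the reported count, not the primary analysis set.

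**The case against.** The strongest reply is that this is a scheduling wrinkle in one visit of a secondary outcome, and much of that stands.

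- **Operating times are not given.** On the T2 rule alone, any operation ending between 06:00 and 08:55 complies. A reader might infer that no patient can comply and that every T2 recording must fail. The article does not support that, because it rests on start times and durations that are not printed.
- **Out of window is not incomplete.** A full 5-min recording taken at the wrong hour is a timing deviation. Section 2.5(3) is engaged only when data are incomplete. A reader might infer that all 202 patients become dropouts. That would need staff to refuse every out-of-window recording and to treat each refusal as incomplete data, and nothing in the article says they will.
- **The primary result is not at risk from this.** It is based on HAMA and analysed by intention to treat with multiple imputation. Section 2.5 asks that dropout be recorded and does not say that the patient leaves the analysis.
- **Between-arm comparison.** Clock time, posture and recent anaesthesia at T2 should affect both randomised arms alike. They add noise but do not bias the between-arm T2 contrast. The article also names no specific T0-to-T2 HRV contrast; its paired tests are listed generically.
- **Condensed article.** Visit tolerances and form fields may sit in the full protocol.

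The last point does not dispose of the matter. The article does not merely omit a tolerance: it prints two rules for the same recording that conflict on most surgical schedules.

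**Conclusion.** The conflict is in the printed text. T2 HRV meets the window only if surgery ends by about 08:55. Holding T1 to the window as well leaves at most 50 min for induction plus surgery, or 15 min with a same-morning T0. Assuming an ordinary daytime list and 60 min or more from induction to the end of surgery, most or nearly all T2 recordings will be out of window or not taken. The exact share cannot be derived from the article.

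What is at stake is the standardisation and completeness of 6 of 36 HRV results, the meaning of any within-arm T0-to-T2 change, and a dropout count that could be inflated for a reason unrelated to the primary outcome. The primary analysis and the between-arm T2 comparison are not undermined. The point is worth an amendment because staff cannot follow both rules as written and recruitment is scheduled to run from August 2025 to August 2026.

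**What to change.** Reconcile Table 1 with section 4.2.2 in one of two ways:

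1. Remove HRV at T2.
2. Exempt the surgery-day recordings (T2, and T1 where needed) from the clock window and the seated rule, and log clock time and posture for each. Compare T2 HRV between arms only, and do not run a paired test of T2 against T0.

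In either case, state in section 2.5(3) that an absent or out-of-window T2 HRV recording does not make a patient a dropout.

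The cost is a short amendment and, under the second option, entries for clock time and posture on the case report form. The downside is that T2 HRV is either lost or kept under conditions that differ from the other visits.
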